| Sample size considerations Anti-diabetic analyses  Sample sizes as per “feasibility counts” section, see table 1(below) for detectable differences in ethnic difference effect sizes. Corresponding to objective i), the proportion prescribed an anti-diabetic at 1 year post-diagnosis (42%) is taken from Sinclair et al (22) (detectable differences calculated using stpower cox command in Stata). Corresponding to objective ii), proportions prescribed metformin as first-line (73%) and a sulphonylurea as second line treatment (87%) are taken from Wilkinson et al (8) (power twoproportions command). Corresponding to objectives iv) and v), mean monitoring rate (2.45 times per year [extrapolated], assuming a SD of 2) (power twomeans command) and probability of treatment intensification at 1 year (24%) are taken from Khunti et al (23) (stpower cox command).  **Table 1. Detectable ethnic differences in outcomes.**   \| **Outcome** \| **Exposure (ethnicity): N vs. N** \| **Detectable ethnic difference effect sizes at α=0.05, β=0.90** \| \| --- \| --- \| --- \| \| Time from diagnosis to first anti-diabetic prescription \| South Asians vs. Europeans:  10.5K vs. 120.4K \| HR: 1.03 \| \| African Caribbeans vs. Europeans:  4.6K vs. 120.4K \| HR: 1.03 \| \| % prescribed metformin first-line \| South Asians vs. Europeans:  10.5K vs. 120.4K \| Difference in proportions: 1.4% \| \| African Caribbeans vs. Europeans:  4.6K vs. 120.4K \| Difference in proportions: 2.1% \| \| % prescribed sulphonylurea second-line \| South Asians vs. Europeans:  3.0K vs. 34.4K \| Difference in proportions: 2.0% \| \| African Caribbeans vs. Europeans:  1.3K vs. 34.4K \| Difference in proportions: 2.9% \| \| Mean monitoring rate, measurements per person year at risk \| South Asians vs. Europeans:  10.5K vs. 120.4K \| Rate difference: 0.07 \| \| African Caribbeans vs. Europeans:  4.6K vs. 120.4K \| Rate difference: 0.10 \| \| Time from sub-optimal diabetes control to treatment intensification \| South Asians vs. Europeans:  10.5K vs. 120.4K \| HR: 1.04 \| \| African Caribbeans vs. Europeans:  4.6K vs. 120.4K \| HR: 1.04 \| \| Time to antihypertensive initiation \| South Asians vs. Europeans:  7.6K vs. 119.4K \| HR: 1.02 \| \| African Caribbeans vs. Europeans:  3.8K vs. 119.4K \| HR: 1.02 \| \| Proportions of eligible people at high recorded CVD risk receiving statins \| South Asians vs. Europeans:  3K vs. 49K \| HR: 1.15 \| \| African Caribbeans vs. Europeans:  2K vs. 49K \| HR: 1.18 \|   Antihypertensive analyses  Sample sizes as per “feasibility counts” section. Little prior data exists in this area, but we can assume a mean time to measurement of 1 month (with an assumed SD of 1 month), as per guidelines for re-measurement after intensification (24). This would give a detectable ethnic difference in time until first monitoring as 0.04 months for South Asians vs. Europeans (using the power twomeans command in Stata), and 0.06 months for African Caribbeans vs. Europeans. Data from Petersen et al (25) suggest that 21% of those eligible for treatment for hypertension in the UK remain untreated. Adding this proportion to the expected numbers commencing antihypertensives by ethnicity (see feasibility count section), we would expect 119.4K Europeans, 7.6K South Asians and 3.8K African Caribbeans to be eligible for time to antihypertensive initiation analyses.  Lipid-lowering medication analyses  Sample sizes as per “feasibility counts” section. Assuming a mean time to monitoring of 3 months (26) and an SD of 1 month, the detectable ethnic difference in time until first monitoring would be 0.04 months for South Asians vs. Europeans, and 0.06 months for African Caribbeans vs. Europeans (using the power twomeans command in Stata). Chidwick et al reported that 24% of the high risk population received statins (21), equating to detectable ethnic differences in proportions receiving statins of HRs 1.18 and 1.15.  All detectable differences fall below what is likely to be considered clinically significant. |

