| N. Exposures, outcomes and covariates *Data sources are listed in square parentheses*  Exposures:  For all objectives, the exposure is either South Asian or African Caribbean ethnicity (defined as above), with European ethnicity as the baseline category. *[Primary care clinical records]*  Health Outcomes by study objective:   1. Proportion of those eligible for primary prevention who are prescribed a) antihypertensives and b) lipid-lowering medication *[Primary care clinical records, prescription drug files]* 2. Time to first anti-diabetic/ antihypertensive/ lipid-lowering medication prescription. *[Primary care clinical records, prescription drug files.]* 3. Choice of a) anti-diabetic (first- to third-line), b) antihypertensive and c) lipid-lowering medications, see appendix for code lists for each (derived from chapters of the British National Formulary). *[Prescription drug files.]* 4. Doses used for each a) anti-diabetic, b) antihypertensive and c) lipid-lowering medication. *[Prescription drug files.]* 5. Monitoring rate, stratified by the time since treatment initiation, e.g. the number of a) HbA1c, b) BP or c) lipid measures divided by the amount of person time, within strata of time since initiation (i.e. first year, second year since initiation etc). *[Prescription drug files, test records.]* 6. Time to treatment intensification after detection of sub-optimal risk factor control. *[Primary care clinical records, prescription drug files, test records.]* Sub-optimal control will be classified as follows:    1. Diabetes; HbA1c≥53mmol/mol (7.5%) (7)    2. Hypertension; blood pressure≥140/80 mmHg, or 130/80 mmHg in those with neuropathy/ nephropathy or retinopathy (24)    3. Lipids; <40% reduction in non-HDL cholesterol (25) 7. Influence of the following on associations between ethnicity and prescribing: smoking, BMI, deprivation, polypharmacy, multi-morbidity, drug adherence (for outcomes iv) and v)), patient engagement with healthcare, diabetes duration and HbA1c. *[Linked IMD data, primary care clinical records, prescription drug files, test records.]*   Covariates (all taken from last entry in medical notes prior to follow-up time commencing)  Age *[Primary care clinical records]*  Sex *[Primary care clinical records]*  Smoking status *[Primary care clinical records]*  BMI *[Primary care clinical records]*  Deprivation (using patient-level IMD scores, with sensitivity analyses using practice-level IMD scores) *[Primary care clinical records, linked deprivation data]*  Polypharmacy (number of medications) *[Prescription drug files]*  Multimorbidity (defined by presence or absence of the following key co-morbidities: coronary heart disease, cerebrovascular disease, heart failure, atrial fibrilliation, hypertension, chronic kidney disease, peripheral arterial disease, retinopathy, neuropathy, cancer [any], COPD/ asthma, severe mental illness) *[Primary care clinical records]*  Patient engagement/ access (using the number of consultations in the year preceding diabetes diagnosis as a proxy) *[Primary care clinical records]*  Patient adherence (using the proportion of days covered: PDC=days of medication supplied per x day period/ x (27)). This will be calculated separately for all medications issued over the follow-up time of interest, and then a mean PDC for all medications will be derived for each patient. Both measures are important as adherence may vary by drug. *[Prescription drug files]*  Disease parameters: baseline HbA1c/ blood pressure and number of years since diabetes diagnosis *[Primary care clinical records, test records.]* |

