| O. Data/ Statistical Analysis For all parts of the study, the population will be people with and without new-onset type 2 diabetes active in CPRD from 2006 (see section K, above) and the exposure will be ethnicity (either South Asian vs. European [baseline] or African Caribbean vs. European [baseline], as detailed in section L, above). Covariates in base models will include age and sex, and further covariates will be considered individually, as outlined in section vi) below. Statistical analysis is further considered by objective:   1. **Outcome:** Proportion of those eligible for primary prevention who are prescribed a) antihypertensives and b) lipid-lowering medication   **Entry:** Date of incident a) hypertension Read code/ raised BP reading or b) elevated 10 year CVD risk score, at least 12 months after study start date of 1^st^ January 2005  **Exit:** First of; date of first antihypertensive/ lipid-lowering medication prescription (defined by the absence of a prescription for the medication in the previous 6 months’ records), end of study, leaving CPRD practice or death  **Analysis:** Proportions receiving antihypertensives/ statin will be compared by ethnicity, then logistic regression models will be used to adjust for confounding/ investigate potential mediators  **Example effect measure:** Odds ratio (OR) of receiving an antihypertensive/ lipid-lowering medication vs. not for each ethnic group of interest, stratified by time period since identification of hypertension/ elevated CVD risk   1. **Outcome**: time to initiation of first-line anti-diabetic/ antihypertensive/ statin, probability of receiving anti-diabetic/ antihypertensive/ statin at one year post-diagnosis/ identification of high CVD risk   **Entry**: date of type 2 diabetes diagnosis/ incident hypertension Read code or raised BP reading/ incident high 10 year CVD risk score recording  **Exit**: date of first anti-diabetic/ antihypertensive/ statin prescription (defined by the absence of a prescription for the medication in the previous 6 months’ records), or end of study/ leaving CPRD practice/ death  **Analysis**: summary statistics will be compared by ethnicity using Kaplan-Meier time-to-event analysis (cumulative failure probability in a given time frame by ethnicity, comparison of medians by log-rank test), Cox proportional hazards regression models will be used to adjust for confounding/ investigate potential mediators  **Example effect measure**: hazards ratio (HR) for anti-diabetic/ antihypertensive/ statin prescription   1. **Outcome:** proportions of patients prescribed medication from each anti-diabetic (stratified by first- to third-line treatment), antihypertensive and lipid-lowering class (defined by the absence of a prescription for the medication in the previous 6 months’ records)   **Sub-population:** a) all participants starting first- to third-line anti-diabetic treatment, b) all patients on antihypertensives, or c) all patients on lipid-lowering medication  **Analysis:** proportions receiving each drug will be compared by ethnicity, then logistic regression models will be used to adjust for confounding/ investigate potential mediators  **Example effect measures**: odds ratio (OR) of being prescribed metformin (=1) vs. non-metformin medication (=0) at first stage of treatment, OR of being prescribed sulphonylurea (=1) vs. non- sulphonylurea medication (=0) at second stage of treatment, OR of calcium-channel blocking antihypertensive prescription vs. non- calcium-channel blocking antihypertensive in those on antihypertensive treatment, OR of statin prescription vs. non-statin lipid-lowering medication prescription in those with >10% 10 year cardiovascular risk   1. **Outcome:** proportions of patients prescribed each dose of each anti-diabetic, antihypertensive and lipid-lowering medication, stratified by treatment stage (defined by the absence of a prescription for the medication in the previous 6 months’ records)   **Sub-population:** a) all participants on first- to third-line anti-diabetic treatment, b) all patients on antihypertensives, or c) all patients on lipid-lowering medication  **Analysis: :** proportions receiving each dose of each drug will be compared by ethnicity, then logistic regression models will be used to adjust for confounding/ investigate potential mediators  **Example effect measures**: OR of being prescribed maximum dose (2g daily) vs. sub-maximum dose of metformin, OR of being prescribed atorvastatin 10mg per day vs. higher doses (20mg, 40mg or 80mg)   1. **Outcome:** yearly monitoring rate post commencement of medication from each anti-diabetic (first- to third-line), antihypertensive and lipid-lowering class – i.e. number of times HbA1c/ blood pressure/ blood lipids measured per person-year of follow-up, stratified by year after commencement; may be multiple entry dates per person for different medications   **Entry:** first use of any medications of interest from 2006 onwards  **Exit:** first of; end of strata (e.g. 1 year after medication commencement), end of study/ leaving CPRD practice/ death  **Analysis:** summary statistics will be compared by ethnicity, Poisson regression modelling used to adjust for confounding/ investigate potential mediators  **Example effect measures**: yearly monitoring rate ratios (RRs)   1. **Outcome:** time to medication intensification (up-titration, addition or switching) after detection of sub-optimal control of diabetes, hypertension or blood lipids, or probability of intensification 1 year post-detection of sub-optimal control; may be multiple entry dates per person for different medications   **Entry:** date when sub-optimal risk factor control detected (see section M for how this is defined for each risk factor)  **Exit:** first of; date of anti-diabetic, antihypertensive or lipid-lowering treatment intensification, end of study/ leaving CPRD practice/ death  **Analysis:** summary statistics will be compared by ethnicity using Kaplan-Meier time-to-event analysis (cumulative failure probability in a given time frame by ethnicity, comparison by log-rank test), Cox proportional hazards regression models will be used to adjust for confounding/ investigate potential mediators  **Example effect measures**: cumulative failure probability for each ethnic group 1 year post detection of sub-optimal value, comparison of median survival times using the log-rank test by ethnicity, HRs of intensification stratified by year   1. **Outcome:** influence of deprivation, polypharmacy, multi-morbidity, drug adherence (iv) and v) only), patient engagement with healthcare, diabetes duration and HbA1c on any ethnic differences found in i) to v).   **Entry:** as above for i), iv) and v)  **Exit:** as above for i), iv) and v)  **Analysis:** as above for i) to v)  **Covariates:** smoking status, BMI, deprivation, polypharmacy, multi-morbidity, drug adherence, patient engagement with healthcare, diabetes duration and HbA1c  **Effect measures:** we will observe the degree of attenuation of the ethnic difference effect measure for each outcome when each covariate is inserted in turn to models, and thus evaluate the likelihood of confounding or mediation  Sub-group/ sensitivity analyses  See section O of original application  Plans for addressing misclassification and bias  See section O of original application  Multiple comparisons  See section O of original application |

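### The HbA1c threshold that starts the diabetes intensification clock is given as two values that are not equivalent: 53 mmol/mol is 7.0%, and 7.5% is about 58 mmol/mol

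*Supplement*

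**What the plan says.** The latest text is the amendment dated 9 December 2019. Its section N (Exposures, outcomes and covariates) lists as outcome 6 "Time to treatment intensification after detection of sub-optimal risk factor control" and then defines sub-optimal control for each risk factor. For diabetes the definition is "Diabetes; HbA1c≥53mmol/mol (7.5%) (7", where the last 7 is the reference number of the diabetes guideline. The same pair stands in the corresponding section of the original application, so the amendment carried it over unchanged.

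Section O (Data/ Statistical Analysis) sets entry to the intensification analysis at the "date when sub-optimal risk factor control detected". The Kaplan-Meier curves, log-rank comparison and Cox models run from that date. One of the example effect measures is "cumulative failure probability for each ethnic group 1 year post detection of sub-optimal value".

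The documents contain no other HbA1c control cut-off, no conversion rule and no statement of which unit takes precedence.

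**The concern.** A threshold written in two units should be one threshold. Here the percentage does not match the mmol/mol figure, so the entry criterion has two readings. The consequences for the diabetes part of the intensification objective are these:

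- **Who is in the risk set.** A person whose HbA1c never goes beyond the range from 53 to about 58 mmol/mol enters under one reading and never enters under the other.
- **Time zero.** A person measured at 55 and later at 60 mmol/mol enters at the first result under one reading and at the second under the other.
- **Which events count.** If that person's treatment was intensified between the two results, the intensification is an event under the lower threshold and falls before entry under the higher one.

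There is also a practical risk. If some results are held in % and others in mmol/mol, applying each printed number to its own unit would put two thresholds into one cohort. The documents do not say how results are stored, so this is a risk and not an established fact.

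The study is declared as hypothesis testing. An entry criterion with two incompatible values leaves a choice that could be made after the data have been seen.

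**Working it through.** **Inputs**

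- Threshold pair: 53 mmol/mol and 7.5% (amendment, section N, outcome 6).
- Unit conversion: % = 0.09148 × mmol/mol + 2.152. This is the standard IFCC/NGSP relation. It is not printed in the documents and is entered here as an assumption. The other common form, mmol/mol = (% − 2.15) × 10.929, was run as a check.

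**Step 1: convert each printed figure**

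- 0.09148 × 53 + 2.152 = 7.00%
- (7.5 − 2.152) / 0.09148 = 58.46 mmol/mol

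The second form gives 6.999% and 58.47 mmol/mol, so the choice of equation makes no difference. The stated equivalence of 53 mmol/mol and 7.5% is not reproduced in either direction.

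**Step 2: allow for rounding**

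| Printed value | Interval that rounds to it | Interval in the other unit |
|---|---|---|
| 53 mmol/mol | 52.5 to 53.5 mmol/mol | 6.95% to 7.05% |
| 7.5% | 7.45% to 7.55% | 57.9 to 59.0 mmol/mol |

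The intervals do not come near each other. The gap is 58.46 − 53 = 5.46 mmol/mol, or 7.5 − 7.0 = 0.5 percentage points.

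**Step 3: gauge how many results the gap covers**

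The documents give no mean or SD for HbA1c. As an assumption, take results to be normal with mean 50, 55, 60 or 65 and SD 10, 14 or 18 mmol/mol. For each combination compute P(53 ≤ X < c), and the same quantity divided by P(X ≥ 53). The cut-off c is first the exact equivalent of 7.5% and then the conventional whole number, 58.

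| Upper cut-off c | Share of all results between the cut-offs | Share of results ≥53 that fall below c |
|---|---|---|
| 58.46 mmol/mol | 10.6% (mean 65, SD 18) to 21.5% (mean 55, SD 10) | 14.1% (mean 65, SD 18) to 48.0% (mean 50, SD 10) |
| 58 mmol/mol | about 10% to 20% | about 13% to 45% |

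These are shares of measurements, not of people. Someone first measured between the cut-offs may exceed the higher one later and still enter, with a later time zero.

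**Step 4: check the link to power**

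The detectable hazard ratio for diabetes intensification in Table 1 rests on a 24% one-year probability of intensification, not on the HbA1c cut-off. The inconsistency therefore leaves the sample-size section as it is.

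**The case against.** The strongest reply is that the plan can be read without difficulty. The inequality sign is attached to 53 mmol/mol and the percentage sits in brackets as a gloss, so 53 governs and 7.5% is a slip. That reading is plausible, but the plan does not state it, and the slip could equally be in the 53. A plan should not depend on a cited guideline to settle its own entry criterion.

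The second reply is that no bias has been shown. Either threshold would apply equally to all ethnic groups, and either gives a coherent cohort. This stands. What is at stake is reproducibility and the definition of the population and time origin, not a demonstrated distortion of the ethnic comparison.

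The third reply is that the scope is narrow. That also stands: the line affects one of three risk factors in one objective. Initiation, choice, dose, monitoring and the blood-pressure and lipid intensification analyses do not use it.

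Finally, the shares of affected results rest wholly on an assumed distribution, and the top of the range comes from a mean of 50 mmol/mol, below both thresholds. They show that the gap could matter; they do not estimate its effect.

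**Conclusion.** The concern holds. The threshold pair is internally inconsistent by 0.5 percentage points, or about 5.5 mmol/mol. The conclusion rests only on the fixed conversion between the two units, and no rounding convention rescues the pair. Because this threshold sets entry and time zero for the diabetes intensification analysis, the cohort for that analysis is not uniquely defined by the plan.

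Under the assumed distributions the gap covers roughly a tenth to a fifth of HbA1c results. No effect on the ethnic hazard ratios can be stated in size or direction. The documents do not show which value was intended. The point should be settled before the cohort is built.

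**What to change.** In section N of the amendment, outcome 6, state one HbA1c threshold with its true equivalent: either at least 53 mmol/mol (7.0%) or at least 58 mmol/mol (7.5%). The choice belongs to the clinical team and should be made before the cohort is extracted. Add a sentence that all HbA1c results are converted to a single unit before the threshold is applied.

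The cost is one line of protocol text and one conversion step in data preparation. The sample-size section needs no change.

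### The adherence score leaves its denominator undefined and averages over all medications issued, so the mean can partly reflect switches, additions and short courses instead of adherence

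*Supplement*

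**What the plan says.** The latest text is the amendment of 9 December 2019 in the Supplement. Section N (Exposures, outcomes and covariates) defines patient adherence by the formula "PDC=days of medication supplied per x day period/ x". On scope and averaging it says: "This will be calculated separately for all medications issued over the follow-up time of interest, and then a mean PDC for all medications" is derived per patient. The drug-level value is kept beside the mean: "Both measures are important as adherence may vary by drug".

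The section does not say what x is, when a drug's denominator starts or ends, or whether only study drugs count. It sets no threshold for poor adherence.

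Section O (Data/Statistical Analysis) puts adherence into the monitoring and intensification analyses only. Covariates enter the models one at a time, and the shrinkage of the ethnic effect is used to judge confounding or mediation. Monitoring follow-up runs to "end of strata (e.g. 1 year after medication commencement), end of study/ leaving CPRD practice/ death". Intensification follow-up runs to "first of; date of anti-diabetic, antihypertensive or lipid-lowering treatment intensification, end of study/ leaving CPRD practice/ death", and intensification includes adding or switching drugs.

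**The concern.** A proportion of days covered measures adherence only if its denominator is the time the patient was meant to be taking the drug. If time before a drug was started or after it was replaced is counted, a change of treatment looks like missed treatment. If a one-week course has the same weight as a year-long drug, the mean depends on how many short courses a patient had.

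This matters because the plan reads attenuation as evidence on mechanism. Polypharmacy is a separate covariate and is not held fixed when adherence is entered alone. A score that partly follows drug count or switching could shrink an ethnic effect and be reported as adherence at work. Noise in the score could also hide a real contribution of adherence. The amendment's Study Background says that South Asian and African Caribbean patients are more likely to be on a higher number of oral diabetes drugs, so the distortion need not be equal across the groups compared.

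**Working it through.** The documents give no adherence figure to reproduce. The check applies the stated formula to hypothetical patients with no gap in supply, whose true coverage is 1.00.

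**Inputs.** Per-drug PDC = days supplied / x, then an unweighted mean over the drugs issued (section N). x = 365 days is an assumption, taken from the one-year monitoring strata in section O. The short course is 7 days from day 100, also an assumption.

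**Readings of the denominator.** A: the whole window for every drug. B: from the drug's first issue to the end of the window. C: the drug's own prescribed interval.

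**Examples.**
- Switch at day 183. A: (183/365 + 182/365)/2 = 0.50, whatever the switch day. B: (183/365 + 182/182)/2 = 0.75.
- Addition at month 9, with a quarter of the year left. A: (1 + 0.25)/2 = 0.625, or 0.63. B: (1 + 1)/2 = 1.00.
- Three long-term drugs plus a 7-day course. A: (1 + 1 + 1 + 7/365)/4 = 0.75. B: (3 + 7/265)/4 = 0.76.
- One long-term drug plus a 7-day course. A: (1 + 7/365)/2 = 0.51. B: (1 + 7/265)/2 = 0.51.

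| Pattern, fully supplied | A | B | C |
|---|---|---|---|
| One drug all year | 1.00 | 1.00 | 1.00 |
| Switch at day 90 | 0.50 | 0.62 | 1.00 |
| Switch at day 183 | 0.50 | 0.75 | 1.00 |
| Switch at day 275 | 0.50 | 0.88 | 1.00 |
| Drug added at day 90 | 0.88 | 1.00 | 1.00 |
| Drug added at month 9 | 0.63 | 1.00 | 1.00 |
| One long-term drug + 7-day course | 0.51 | 0.51 | 1.00 |
| Three long-term drugs + 7-day course | 0.75 | 0.76 | 1.00 |
| Four long-term drugs + 7-day course | 0.80 | 0.81 | 1.00 |
| Two long-term drugs + three 7-day courses | 0.41 | 0.42 | 1.00 |

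**Reading C has the opposite weakness.** A patient half-covered on the only long-term drug (0.50) who also has a fully supplied 7-day course (1.00) scores (0.50 + 1.00)/2 = 0.75. If short courses are included, poor adherence is diluted.

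**Where it acts.** Monitoring strata do not end at a switch or an addition, so both fall inside the window. Intensification follow-up ends at the first such change in the studied class, so there the distortion comes mostly through drugs outside that class.

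**The case against.** The strongest reply is that x is only a placeholder. The phrase about follow-up time may say which medications are scored, not how long each denominator is. Under each drug's own interval every fully supplied patient scores 1.00. That stands: the whole-window denominator is an inference. It does not clear the plan, because nothing in the text selects that interval, and even then averaging in short courses masks poor adherence.

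The cited source might settle the rule. In the amendment's reference list, however, number 27 is the diabetes algorithm paper. In the original application that number was a paper on measuring concurrent adherence to several related medications, whose rules are not given in the documents.

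The phrase on all medications could mean all study medications, since the appendix lists medication codes only for diabetes, antihypertensive and lipid-lowering drugs. If so, the short-course examples fall away, but switches and additions are still lowered under A, and switches under B.

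Three stronger readings are tempting and go too far:
- A reader might infer that adherent patients are classed as poorly adherent. There is no cut-off, and some losses are modest (0.88 for an early addition, 0.80 for four long-term drugs plus a short course).
- A reader might infer that early refills push the score above 1. Seven 60-day supplies give 420/365 = 1.15, but issued on time at days 1, 61, and so on to 361, the excess is only the last supply running past day 365. Counting supply inside the window gives 365/365 = 1.00.
- A reader might infer that both outcomes are equally affected. The end-of-follow-up rule for intensification argues against this.

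The plan also keeps the drug-level PDC, which short courses and additions of other drugs do not dilute, although its denominator is equally undefined. The original application admits that PDC is a proxy, but only because dispensing and intake cannot be verified.

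**Conclusion.** The point holds in this form: the denominator is undefined, the mean runs over all medications issued, and none of the three plausible readings makes that mean a clean measure of adherence. Under the most natural one, true coverage of 1.00 is scored between 0.41 and 0.88 in the patterns of switching, adding or short courses shown. Starting the denominator at first issue mends additions only. Using each drug's own interval removes the loss but lets short courses hide non-adherence.

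These figures assume x = 365 days and hypothetical patients. The short-course figures also assume that unrelated drugs are included. The documents give no frequencies of switching or short courses by ethnicity, so the resulting bias in any ethnic effect cannot be sized. The consequence is limited to interpreting attenuation, mainly in the monitoring models. It is worth correcting before analysis, but it does not threaten the main comparisons.

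**What to change.** Rewrite the adherence definition in section N as follows:
- Numerator: distinct calendar days with supply that fall inside the window, so the score cannot exceed 1.
- Denominator: days from the first issue in the window to the recorded stop, the replacement, or the end of the window.
- Drug set: only the anti-diabetic, antihypertensive or lipid-lowering drugs relevant to the outcome being modelled.
- Level: score by class, a day being covered if any drug of the class is in hand, so a within-class switch is not a gap. Average over those classes.

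Under this rule a seamless within-class switch scores 365/365 = 1.00. A fully supplied month-9 addition also scores 1.00, and a short course of an unrelated drug no longer enters.

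State the measurement window at the same time. The section's general covariate rule, "Covariates (all taken from last entry in medical notes prior to follow-up time commencing"), does not fit a score taken over follow-up. Correct the citation number too.

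The cost is wording and derivation code; no new data are needed. One small downside is that class-level scoring hides non-adherence to a single drug within a class, so keep the drug-level PDC, with the same numerator and denominator rules, as the secondary measure.
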